The **second screening visit** (study visit 2) takes place two to four weeks before the first planned injection. This visit will include review of all laboratory results. At this visit the study nurse confirms that the volunteer fulfils all the inclusion criteria, including laboratory results, makes an abbreviated risk assessment and a brief summary of the study design. Reassurance has to be made that the study volunteer fully understands the concept of the study. The results of the screening investigations will be reviewed and volunteers who are still eligible and willing will be asked to donate blood samples for baseline immunogenicity and complete part 2 of the Informed consent (*Appendix ii/iv, CRF 4-II*). Volunteers will also be reminded that they are free to end all obligations in the study whenever they wish and that a premature termination will not have any negative influence in future contacts with the clinic. If no contraindications are revealed volunteer will be asked to donate blood for first baseline immunogenicity tests.

The volunteer will then be randomized into one of the study arms. At randomization a total of sixty sealed plain envelopes containing an equal number of assignments to groups I, II and IIIa & IIIb, will be prepared and put in the box. Group numbers refer to the immunization schedule.

The study Pharmacist will take the prepared envelopes and put them in the box that is kept under lock. Volunteers accepted into the study will be randomized by a Pharmacist through CRF7-I, by selecting the next consecutive envelope containing the vaccine or placebo assignment in accordance with the generated randomization list. This will be documented in CRF 7-II.

The Pharmacist will then inform the Study Nurse at the clinic of the randomization group of the volunteer (ID or IM) on a copy of CRF 7-I, including a number of the envelope, but will not inform on whether this is vaccine or placebo. The Study Nurse will record the envelope number and the IM/ID assignment into a Register book, the medical record file (source document), as well as the outer cover of the volunteer's file.

The pharmacist will then deliver to the nurse the appropriate vaccine/placebo that corresponds to the assigned group.

Recruitment of volunteers will be staggered so that a maximum of 3 volunteers per week will enter the trial during the first 5 weeks.

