### **Study Procedures**

At **week 0 (study visit 3)** the study volunteer again meets both study nurse(s) and study doctor(s). Once again confirmation has to be made that the volunteer fulfils all inclusion criteria, including laboratory results, and fully understands the concept of the study. After doing so blood is donated for second baseline immunogenicity tests. Urine for pregnancy test will be performed and found negative.

The volunteer will then receive the first injection according to the assigned study arm. The study visit will be documented in study form CRF 8-I (*Appendix xii*). Following injection volunteers will be observed for 30 minutes for acute adverse reactions and will also be contacted the day following injection by the study nurse for a brief adverse reaction interview. In addition, volunteers will complete diaries (*Appendix xvii {Form 7}*) over events for 7 days following each vaccination and receive telephone numbers to call 24 hours a day, in order to get in contact with the study personnel if needed. A folder with diary cards, disposable thermometers and a ruler will be issued to each volunteer.

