### **Cellular responses**

The assessment of primary cellular responses will be achieved by determining the following HIV-1 specific cellular immune responses:

- CD8 and CD4 T helper cell responses
  - IFN- $\gamma$  ELISPOT and Interleukin-2 assay (on stored Peripheral Blood Mononuclear Cells (PBMC's)), including determination of cross clade responses, using pools of overlapping peptides representing env, gag and pol proteins
  - Intracellular cytokine staining (ICS) for IFN- $\gamma$  and Interleukin-2 (IL-2) (ref 27) using the same peptide pools as in the ELISPOT and testing both for CD8 and CD4 T cell responses
- CD4 T helper cell responses
  - Lymphocyte proliferation assay (LPA) to the immunizing antigens and mitogens on fresh PBMC's
    - Standard assay: measurement of proliferation by uptake of  $^3\text{H}$ -thymidine
    - New assay: whole blood flow-cytometric assay (FASCIA=Flow-cytometric Assay of Specific Cell-mediated Immune response in Activated whole blood) developed at SMI. Both CD4 and CD8 T cell responses can be demonstrated by this method.
- CD8 T cell response
  - Cytotoxic T lymphocytes (CTL) by chromium release assay

Interferon-gamma Enzyme-linked immunospot (ELISPOT) will be used as a standard assay to monitor HIV cellular immune response in vaccinated individuals and will be performed on fresh PBMC's. These procedures will be validated prior to the trial. Individuals with <50 SFC/million PBMCs will be regarded as non-responders. If the average value of sample wells is >4 times the

background (medium only) and >55 SFC/million PBMCs the individuals will be regarded as responders.

A new whole blood flow-cytometric assay (FASCIA=Flow-cytometric Assay of Specific Cell-mediated Immune Response in Activated whole blood) developed at SMI will also be performed later on stored PBMCs. Both CD4 and CD8 T cell responses can be demonstrated by this method. Quality control and exchange of specimens with international laboratories will be performed.

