### **Immunogenicity Data**

Immunogenicity endpoints will be compared formally at week 0, 10 and 12, according to study dosing group. Binary endpoints will be compared using Fischer's exact test. Continuous endpoints will be compared using 2-sample t-tests or non-parametric equivalents as appropriate to the data.

Immunogenicity of the candidate vaccine will be determined based on comparisons between study treatment arms. Associations between immunogenic endpoints will be assessed using multivariate regression models.

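### The ELISPOT responder rule ignores the two pre-vaccination samples, so lasting baseline reactivity counts as a response, inflating per-arm rates and diluting arm contrasts

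*Protocol*

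**What the plan says.** Under Cellular responses, the protocol fixes numeric limits for the IFN-gamma ELISPOT. The lower one is "Individuals with <50 SFC/million PBMCs will be regarded as non-responders". The responder condition begins "If the average value of sample wells is >4 times the" and continues "background (medium only) and >55 SFC/million PBMCs the individuals will be regarded as responders". The only comparator is the medium-only well of the same assay, joined to an absolute cut-off.

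Two pre-vaccination samples exist. At the second screening visit (study visit 2), two to four weeks before the first injection, the "volunteer will be asked to donate blood for first baseline immunogenicity tests". At week 0, before the injection, "blood is donated for second baseline immunogenicity tests".

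Baseline results have two stated uses. Volunteer characteristics provides for a summary of baseline values by arm. Immunogenicity Data states: "Immunogenicity endpoints will be compared formally at week 0, 10 and 12, according to study dosing group". The same section sends binary endpoints to Fisher's exact test and bases the judgement of immunogenicity on comparisons between arms. No section requires a negative baseline, a rise over baseline, or separate handling of volunteers reactive at baseline.

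The list of primary end-points in Statistical considerations includes IFN-gamma ELISPOT in item 2, which concerns the immune responses that the immunization schedules elicit.

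**The concern.** Medium-only wells contain no peptide. They correct for spontaneous spots, not for recognition of env, gag or pol peptides that was there before vaccination. The rule therefore records whether a volunteer is reactive at a visit, whereas the endpoint asks whether immunization produced the reactivity.

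The resulting yes/no variable is what Fisher's test analyses. Volunteers who were reactive beforehand raise the responder percentage in every arm, placebo included. That shrinks the differences the trial is meant to show, with only 20 volunteers in each vaccine arm. The samples needed to remove the problem are already being collected.

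**Working it through.** The protocol gives no power calculation and no baseline ELISPOT rate, so there is no figure of its own to reproduce. The size below is an illustration.

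**Inputs from the protocol.** Arms I and II have 20 vaccinees each; IIIa and IIIb have 10 placebo recipients each, 20 together. Binary endpoints are compared by Fisher's exact test.

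**Assumed inputs.**
- b, the proportion above both limits before vaccination: 2%, 5% or 10%. Reactivity is taken to persist and to be independent of induction.
- t, the truly induced rate: 40%, with 30% as a check.
- Two-sided alpha of 0.05.

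**Apparent responder rates under the present rule.** Vaccine arm: t + (1 - t)b. Placebo: b. At t = 40%, the vaccine rate reads 41.2%, 43.0% and 46.0% for b = 2%, 5% and 10%.

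**Misclassified volunteers.** A pre-reactive vaccinee is misclassified only if the vaccine would not have induced a response anyway. The expected number is 40(1 - t)b + 20b. At t = 40% this is 24b + 20b = 44b, that is 0.88, 2.2 and 4.4 of 60.

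**Rates if baseline-positives count as non-responders.** Vaccine arm: t(1 - b), that is 39.2%, 38.0% and 36.0% at t = 40%. Placebo: 0. True responders lost among 40 vaccinees: 40tb = 16b, that is 0.32, 0.8 and 1.6.

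**Exact power**, summing the binomial probabilities of all tables with Fisher p at or below 0.05, one vaccine arm (20) against all placebo (20):

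| t | b | Present rule | Baseline-positives as non-responders |
|---|---|---|---|
| 40% | 2% | 0.88 | 0.94 |
| 40% | 5% | 0.78 | 0.93 |
| 40% | 10% | 0.65 | 0.90 |
| 30% | 2% | 0.67 | 0.74 |
| 30% | 5% | 0.55 | 0.72 |
| 30% | 10% | 0.41 | 0.66 |

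At b = 0 the two rules agree, with power 0.95 at t = 40% and 0.76 at t = 30%. If both vaccine arms are pooled (40 vs 20, t = 40%), the present rule gives 0.98, 0.92 and 0.82, so the loss is smaller there.

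**i.m. against i.d.** With induced rates t1 and t2, the apparent difference is (t1 - t2)(1 - b). A true difference of 20 points would read as 20 x 0.90 = 18 points at b = 10%.

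**The case against.** The strongest reply is that the rule only classifies an assay read-out. The vaccine effect is judged by comparing randomised, blinded arms that include 20 saline recipients, and the week 0 comparison and baseline summary would reveal pre-existing reactivity at group level. This stands as far as direction goes: the contrast is diluted and not tilted towards the vaccine. It does not correct any individual's classification, and the per-arm percentages stay inflated.

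The 2-10% range is indeed an assumption. Volunteers are HIV-negative, low-risk and have had no HIV candidate vaccine, so the rate may be near zero, and the effect with it. Reactivity that fades before the later visit also reduces it. If the induced rate after boosting were near the 34 of 37 (92%) reported from the Swedish trial, a vaccine arm would be inflated by only about 0.08b, or 0.2-0.8 points.

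Details of visits and pools may sit in an analysis plan that is not shown. But the protocol itself states the cut-offs and the comparator, so the definition is fixed here, without baseline.

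Two stronger readings are tempting. One is that each baseline-reactive volunteer adds a full 5 points to a 20-person arm. That holds only for someone the vaccine would not have converted. The other is that the interim 19 of 46 ELISPOT responses lose their meaning because baseline is ignored. That figure has no breakdown by arm, so it cannot be read as vaccine take under any responder rule, and it is no evidence on this point.

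**Conclusion.** The point holds as a defect in how a primary-endpoint variable is defined. A volunteer reactive before the first injection who remains so is counted as a responder, and nothing in the protocol prevents it. The consequence is inflated per-arm responder percentages and weaker vaccine-placebo and i.m./i.d. contrasts. The documents do not support a claim of bias in favour of the vaccine.

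Under the stated assumptions, with a 40% induced rate, the size is about 0.9-4.4 misclassified volunteers of 60, and power of 0.88-0.65 against 0.94-0.90 in a 20 vs 20 comparison. The true size is unknown because no baseline rate is given. The change is worth making because it is cheap and, at each assumed rate, raises power even in this strict form.

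**What to change.** Before unblinding, amend the rule as follows:

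- A volunteer is a responder to a pool only if the positivity criteria are met after vaccination and were not met for that pool at baseline. State in advance how the two baseline samples are combined when they disagree; letting one positive sample decide is the strictest choice and costs the most true responders.
- Volunteers positive at baseline count as non-responders for that pool in the main analysis.
- Repeat the analysis under the present rule as a sensitivity analysis.
- Report the number of baseline-positive volunteers by arm.

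No new visit or blood draw is needed. The costs are slightly lower responder rates, the loss of a few true responders who were baseline-positive (0.3-1.6 of 40 vaccinees in the illustration), and a change of definition after blinded interim ELISPOT results were seen. The amendment should record that timing and its reason. If no volunteer is baseline-positive, the results do not change and the report can say so.

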#### **Storage of Cellpellets for HLA testing**

Lymphocyte cellpellets will be stored at MUHAS department of Microbiology/Immunology for later HLA typing that will be performed by molecular methods at a laboratory to be identified later.

### ***OTHER ASSESSMENTS***

#### **HIV testing**

Samples will be tested at MUHAS, department of Microbiology/Immunology using HIV antigen/antibody ELISA, and discordant results will be confirmed by a Western blot Inno-Lia immunoblot according to standard operating procedures.

#### **Antibodies against Vaccinia**

Serum samples will be stored at MUHAS, department of Microbiology/Immunology for later testing.

#### **Following adverse event**

Other assessments may be performed as clinically indicated due to an adverse event.

### **CONCOMITANT MEDICATION**

Volunteers will be asked about medication taken at each visit up to and including week 18, and this will be recorded in the case record form. Thereafter, they will be asked about medication only in relation to adverse events reported. It is expected that the name of the drug, indication for use, dose, frequency, start and stop dates will be available either from the volunteer or from the prescribing physician. For medication available over the counter or other sources, the maximum information available on questioning the volunteer will be recorded.

### **ADVERSE EVENTS**

Volunteers will be provided with a diary card, disposable thermometers and ruler at the immunizations.

#### **Definitions**

An adverse event is any adverse experience occurring during the course of the study including the screening period. Criteria for grading clinical and laboratory events are listed in ***appendix xiv***. The severity of events reported on the adverse event form will be determined by the investigator, based on the Toxicity Grading Scale or if the event is not listed the event will be graded following these guidelines:

- Mild (Grade 1): Transient or mild discomfort. No limitation in normal daily activity.
- Moderate (Grade 2): Some limitation in normal daily activity.
- Severe (Grade 3): Unable to perform normal daily activity.
- Serious (Grade 4): Life threatening
- Death (Grade 5): Death

A severe adverse event is one **graded 3 or 4** by criteria in *appendix xiv*. Some, but not all grade 3 and 4 adverse events will be “serious” by ICH GCP criteria below.

### **Serious Adverse Events (SAEs)**

An adverse event is considered to be a “serious adverse event” by ICH Good Clinical Practice (ICH GCP) criteria if it results in the following:

1. Death,
2. A threat to life,
3. Requires in-patient hospitalization or prolongs existing hospitalisation (hospitalisation for elective treatment of a pre-existing condition is not included),
4. Results in persistent or significant disability or incapacity,
5. Is a congenital anomaly (i.e. the outcome of pregnancy involving a volunteer),
6. Is any other important medical condition\*.

\*Examples of conditions regarded as “any other important medical condition” include allergic bronchospasm requiring intensive emergency treatment, seizures or blood dyscrasias which did not result in hospitalisation or development of drug dependency.

### **Relationship of adverse events to study product**

This can be classified as:

- None:** Adverse events felt to be due to extraneous causes that neither follow a known pattern of response nor a reasonable temporal relationship to study product.
- Remotely related:** Adverse events that are unlikely to be related to product but which follow a reasonable temporal relationship, such that this cannot be completely excluded or events that could be associated with product but which are unrelated in time.
- Possibly related:** Adverse events that may be due to extraneous causes but which follow a known pattern of response and/or a reasonable temporal relationship to study product.
- Probable:** Adverse events that cannot be explained by extraneous causes; which follow a known pattern of response and/or a reasonable temporal relationship; which disappear or decrease on cessation of study product and reappear on re-challenge.

### **Reporting adverse events**

Adverse events should be recorded on the appropriate case record form (CRF 8-III). Any grade 3 or 4 adverse event (see *appendix xiv*) or any event resulting in discontinuation of the vaccination schedule should be reported within 2 working days to the DSMB for review and appropriate recommendations. The proposal as to whether continue or discontinue the study will be submitted to the monitor, TCC, NIMR and TFDA for further review and action

**Serious adverse events** should be reported to the monitor the same working day that the Clinical Investigator becomes aware of the event fulfilling the above criteria. This can be done by telephone, e-mail or fax. The minimum criteria required in reporting a SAE are the volunteer identifiers (trial number/ date of birth/initials), reporting source (name of Investigator), and why the adverse event is identifiable as serious. The adverse event reporting telephone/ fax number for MUHAS is [name] (HIVIS office). The address for reporting to the monitor will be determined by the study monitor.

The monitor will confirm that the event is potentially reportable and arrange for urgent review of the case by the TCC within 2 working days. Should the case be considered reportable by this group, a report will be prepared by the clinical investigator or his deputy and filed with the TFDA and the DSMB. The Principal Clinical Investigator is responsible for notifying the Local Research Ethics Committee.

Examples of SAEs that do not require expedited reporting include:

1. Hospitalisation for scheduled surgery unrelated to vaccine, other than temporally (within 30 days).
2. Orthopaedic or traumatic injuries requiring hospitalization.
3. Hospitalisation planned for pre-existing conditions not due to an aggravation in the condition.
4. SAEs occurring more than 30 days after vaccination or having appeared before vaccination without any aggravation after vaccination

### **DISCONTINUATION PROCEDURES (including withdrawal and stopping participation in the study)**

Volunteers may withdraw at any time if they wish to do so, for any reason. The date of withdrawal and reason for doing so should be recorded in the appropriate case record form. The clinical investigator may decide that it is not in the best interests of the volunteer to proceed to the next immunisation following an adverse event (see below). The discontinuation and reason should be recorded in the appropriate immunisation and reportable adverse event case record forms, which should be forwarded to DSMB within the next 2 working days. Trial visits should carry on at least until resolution or stabilisation of the event, but ideally up to the last visit in the schedule, provided the volunteer is willing. The frequency of visits and laboratory investigations may be reduced on consultation with the Principal Investigator or Trial Management Group

### **Criteria for withdrawal of volunteers from injection schedule**

Under certain circumstances, a volunteer will be terminated from participating in further injections. These events include:

1. HIV infection

2. Pregnancy
3. Grade 3 or 4 systemic events classified as probably or definitely associated with immunization (with the exception of grade 2 nausea, headache or myalgia).
4. Type 1-hypersensitivity associated with immunization.
5. Serious intercurrent illness that is not expected to resolve prior to next scheduled immunization.
6. Need for systemic glucocorticoids or other immunomodulators than NSAIDs for any reason.
7. Repeated failure to comply with protocol requirements.
8. The Sponsor, vaccine provider or principal investigator decides to stop or cancel the study.
9. The NIMR and or MUHAS ethical committee decides that the study be stopped

Trial volunteers who are discontinued from additional study injections will continue to be followed according to the schedule to further evaluate safety and monitor adverse events. They will also continue to be covered by the medical insurance till the end of the study period.

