## END POINTS

### Primary

#### *Safety*

The safety of immunization with the seven DNA plasmids carrying HIV-1 genes will be assessed by *clinical features as well as standard biochemical and haematological laboratory tests*. Any worsening of the severity grade will be considered for causality with the vaccine.

The alternative routes of immunization (intramuscularly and intradermally with the Bioject device) will be evaluated by assessing local (pain, cutaneous reactions including induration), general (fever, chills, headache, nausea, vomiting, malaise, myalgia) and other unsolicited adverse events on vaccination day and within 7 days. Any grade 3 or 4 event will be taken as an indication that the arm is less tolerable.

The primary safety parameters will be graded according to *appendix xiv*, and are:

1. Local adverse event Grade 3 or above (pain, cutaneous reactions including induration)
2. Systemic adverse event Grade 3 or above (temperature, chills, headache, nausea, vomiting, malaise, and myalgia)
3. Other clinical or laboratory adverse event Grade 3 or above confirmed at examination or on repeat testing respectively

Tests for possible toxicity due to vaccination will include: Liver function tests, renal function tests and full blood picture. Any event attributable to vaccine leading to discontinuation of the immunization regimen must be documented.

Data on local and systemic events listed above will be solicited with specific questions or using a diary card for a minimum of 7 days following each immunization. Data on other clinical events and laboratory events will be collected with an open question at each visit and through routine scheduled investigations respectively.

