#### **Criteria for stopping the study**

1. The Principal investigator will closely monitor and analyse study data as it becomes available and will make determinations regarding the presence and severity of the adverse events
2. Any grade 3 systemic event assessed by DSMB as possibly, probably or definitely related to the vaccination (following exclusion of other unrelated common causes) or if one volunteer experiences grade 4 or 5 (death) SAE assessed as possibly, related to the vaccination.

The study injections and enrolments would resume only after review of the adverse events by the DSMB and a decision by the TCC including the Chairman resulted in a recommendation to permit further study injections and study enrolments. Safety data and changes in study status will be submitted to the ethics committee.

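### Read literally, the mandatory withdrawal rule for related grade 3–4 systemic reactions cannot act on a first reaction, because the relatedness category it needs requires recurrence on re-dosing

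*Protocol*

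**What the plan says.** Protocol, Criteria for withdrawal of volunteers from injection schedule, item 3, ends further injections for "Grade 3 or 4 systemic events classified as probably or definitely associated with immunization (with the exception of grade 2 nausea, headache or myalgia").

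The section Relationship of adverse events to study product defines four categories: none, remotely related, possibly related and probable. Probable applies when no outside cause accounts for the event and it fits a known pattern or a plausible timing. The definition then adds events "which disappear or decrease on cessation of study product and reappear on re-challenge". There is no definite category.

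Three other provisions bear on the same volunteer:

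- Reporting adverse events: any grade 3 or 4 event "should be reported within 2 working days to the DSMB for review and appropriate recommendations".
- Discontinuation procedures: the clinical investigator may conclude that "it is not in the best interests of the volunteer to proceed to the next immunisation following an adverse event".
- Criteria for stopping the study: the trigger includes "Any grade 3 systemic event assessed by DSMB as possibly, probably or definitely related to the vaccination". Injections resume only after DSMB review and a decision by the Trial Coordinating Committee.

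On grades, the Definitions section separates "Moderate (Grade 2): Some limitation in normal daily activity" from "Severe (Grade 3): Unable to perform normal daily activity". The primary safety parameters include "Systemic adverse event Grade 3 or above (temperature, chills, headache, nausea, vomiting, malaise, and myalgia").

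The immunization schedule gives DNA at weeks 0, 4 and 12 and MVA at weeks 36 and 80.

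**The concern.** Apart from the item on type 1 hypersensitivity, item 3 is the provision that removes discretion after a serious systemic reaction to the vaccine: once an event qualifies, that volunteer receives no more injections. It qualifies only through a relatedness rating, and the rating is defined partly by what happens at the next injection. The rule exists to prevent that next injection, so the definition makes the safeguard wait for the exposure it is meant to avoid.

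At stake is whether a volunteer who has had a related grade 3 or 4 systemic reaction is withdrawn by rule or by case-by-case judgement. The question is live because the amendment adds a second MVA injection, for which volunteers are to give fresh consent.

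**Working it through.** No figure in the plan is in dispute, so the check sets the provisions side by side.

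**1. When can a first reaction reach probable?** Take the definition as conjunctive, as its wording reads, and take re-challenge to mean another dose of the same product. Injection weeks are from the immunization schedule.

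| First reaction after | Earliest re-challenge | Injections still preventable once it recurs |
|---|---|---|
| DNA 1 (week 0) | DNA 2 (week 4) | DNA 3, MVA 1, MVA 2 |
| DNA 2 (week 4) | DNA 3 (week 12) | MVA 1, MVA 2 |
| DNA 3 (week 12) | none with DNA | probable never reached |
| MVA 1 (week 36) | MVA 2 (week 80) | none |
| MVA 2 (week 80) | none | none remain in any case |

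In every row where an injection could still be withheld, the rule either acts one dose late or does not act. For MVA the gap is 80 − 36 = 44 weeks and the only re-challenge is the final injection, so the rule can never act in time. If re-challenge is read more widely as any later study injection, a DNA 3 reaction could be confirmed at MVA 1, leaving MVA 2 to withhold. The MVA 1 row does not change.

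**2. Do the relatedness terms match?** Item 3 accepts two terms. *Probably* corresponds to probable; *definitely* has no counterpart on the scale. Because the terms are joined by *or* and probable is already the top category, the undefined term adds and removes no one. It does not rescue the rule either, since there is no defined route to it.

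**3. What do the other provisions oblige?**

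- DSMB reporting obliges notification and review.
- The discontinuation section permits the investigator to withhold a dose.
- The stopping criteria pause the study at a lower relatedness level (possibly), then state when injections and enrolments may resume. They do not say whether the affected volunteer is re-injected.

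None of the three mandates ending that volunteer's injections.

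**4. What does the parenthesis do?** The rule covers grades {3, 4} and the exception covers grade {2}. The overlap is empty, so the printed rule equals the rule with the parenthesis deleted. Listed symptoms are graded by appendix xiv, which is not in the text available, but this step needs only that grades 2 and 3 are different grades.

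**5. How many injections are governed?** By design 20 + 20 = 40 volunteers receive vaccine and 10 + 10 = 20 receive saline, so at most 40 + 20 = 60 second MVA/placebo injections. This is a ceiling, because the second boost needs new consent. The protocol states no rate of related grade 3–4 systemic reactions, so no expected number can be derived.

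**The case against.** The strongest answer is that no such volunteer slips through. Every grade 3–4 event goes to the DSMB within 2 working days. A grade 3 systemic event rated even possibly related pauses injections. The investigator can withhold the next dose. The Trial Coordinating Committee has the final say on grade and relatedness, and the withdrawal list is introduced as inclusive, so it need not be exhaustive. An assessor might also treat the re-challenge clause as a description of the typical case, to be applied only where re-challenge happened. The interim account is reassuring too: 26 first MVA/placebo injections with no untoward effect, and three serious adverse events in the trial, all judged unrelated. Those data are pooled over vaccine and placebo.

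Most of this stands, and it rules out a stronger reading. A reader might infer that a volunteer could be re-injected after a severe related reaction without anyone looking at the case. The documents do not support that.

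A reader might also infer from the grade 2 parenthesis that the withdrawal threshold is indeterminate, and try to count the symptom and grade combinations on which possible rewordings disagree. That is not supported either. The printed rule is determinate at grade 3–4, no section states the alternative rewordings, and such a count would not measure impact. Nor does the missing definite category leave anyone out.

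What the objection does not answer is the re-challenge clause. Review, discretion and a study-level pause are not a mandatory individual rule, and a sensible assessor has to set aside the printed definition for item 3 to work.

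**Conclusion.** The point holds as a defect in the wording of a mandatory safety rule. Read literally, item 3 cannot end injections after a first related grade 3–4 systemic reaction. For a first reaction to MVA it cannot act before the last injection. The consequence is that the decision falls to case review; it does not escape review.

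The practical effect is probably small and cannot be quantified from the protocol. The ceiling is 60 second MVA/placebo injections, 40 of them vaccine. No endpoint, sample size or error rate is affected.

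The conclusion assumes that the clauses defining probable are cumulative, and that appendix xiv, not available here, does not restate the relatedness criteria. The empty parenthesis is secondary. Naming only three of the seven listed systemic symptoms suggests that some distinction was intended, but the document does not show which.

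**What to change.** Make these changes in the current amendment, before the second MVA is given:

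1. In Relationship of adverse events to study product, state that recurrence on re-challenge is supportive evidence and is not required for a probable rating. Alternatively, extend withdrawal item 3 to events possibly or probably related, which matches the relatedness level in the stopping criteria. The first option corrects the fault at its source; the second casts a wider net.
2. Delete *definitely* from item 3 and from the stopping criteria, or define it on the scale.
3. Ask the sponsor and the DSMB whether a grade 2 threshold or a grade 3 exception was meant in item 3, and print the confirmed grade. If neither was meant, delete the parenthesis. Deletion changes no withdrawal decision relative to the printed text.

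The cost is a few lines of wording, with no added visits or procedures. The downside is that a few more volunteers may be withdrawn from the second MVA after a related first reaction. They would miss that boost but remain in scheduled safety follow-up, as the protocol already provides.
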